### The intervention (the incremental HD regime)

Participants in the intervention group will receive incremental HD using a novel approach, starting therapy on twice-weekly basis with progressive increases in the duration and frequency of sessions over 15 weeks, achieving conventional treatment times by the end of this period.

The treatment delivered will comprise of a ‘start’ phase, representing just the first 2 days of dialysis (this is similar to conventional start), followed by 3 incremental phases or steps (also see Fig. 2):Start (phase 1): (first 2 days of HD): day 1, 2-h HD session; day 2, 3-h HD session.Phase 2: twice-weekly 2-h long dialysis sessions for 2 weeks.Phase 3: twice-weekly 3-h long dialysis session for 6 weeks.Phase 4: three-times weekly 3-h long session for 6 weeks.

Following this, participants will continue long-term HD as per clinical requirements. The regime includes several safety elements including frequent fluid status monitoring (through clinical examinations and bio-impedance analyses) and regular potassium testing. Clinicians and dialysis nurses can override the regime at any point if clinically indicated.

The regime tested here has been developed by the study investigators ([name], SB) in consultation with patient groups as a pragmatic way of reducing exposure to dialysis during the critical early transitional period. At the designing stage, patient engagement involved discussions with National Institute of Health Research (NIHR) patient research ambassadors for renal medicine at our centre and the members of Hull Kidney Patients Association (HKPA). In addition, a brief questionnaire was given out to 20 current HD patients to gauge their opinions on the current proposals. Patient feedback was very positive; patients particularly appreciated the focus on maintaining independence at the start of HD which they valued highly. HKPA members saw this as a much-needed advancement in dialysis therapies and felt that patients will be motivated to help. The group gave positive suggestions on how to narrow down the process of identifying potential participants e.g., by prioritising the sub-set of patients who were being referred for vascular access procedure (as they are the most likely patients to start dialysis soon). In the survey of 20 HD patients, 10 patients responded 7 of whom indicated that they would have taken part in the study if they had the opportunity.

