#### Weights and blood pressures

Weight and blood pressure (BP) readings will be monitored at baseline and then at each subsequent dialysis visit. These will be measured pre- and post-dialysis. Inter-dialytic weight gain (IDWG) or loss will be recorded. BP readings taken during dialysis (intra-dialytic BPs) will also be recorded.

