#### Safety and adverse events data

There are several safety measures built-in to our incremental HD program to protect patients from the deleterious effects of a rapid decline in RRF around the time of dialysis initiation or when at least three-times weekly dialysis is needed from the start. First, we are only recruiting patient with planned out-patient dialysis start; this excludes the majority of those who develop critical or life-threatening issues related to CKD-5. Furthermore, all participants are reviewed at the start (see study procedures in supplementary table S1) to ensure safety before patients commence the program. During the program, patients receive regular visits from the study team (in the first month, five study related checks are undertaken including review by the study medic on four occasions). Also, clinicians can change the dialysis schedule e.g., offer extra dialysis or to take the patient off the program completely at any point during the study; for this reason, the mid-week dialysis slot is always kept open in case a participant needs additional dialysis. Finally, this a short incremental regime lasting just over 3 months; hence, a decline in RRF is anticipated and treatment increases are pre-emptive in this program.

Information related to adverse events (AEs) and serious adverse events (SAEs) will be recorded continuously throughout the study based on definitions presented in supplementary table S2. Routinely, all dialysis treatments are recorded in the local dialysis treatment database and a named nurse documents a narrative account of that day’s treatment making notes of any significant events. This information will be accessed by the study team and interrogated for AEs and SAEs and substantiated with information documented elsewhere in patients’ electronic health records. Compliance with the programme and adherence (or deviations) to the prescription will be monitored.

Intra-dialytic hypotension is common and affects 17% of all dialysis sessions [39]. We define IDH in accordance with the European Best Practice Guidelines [40] as a symptomatic drop in BP during dialysis of ≥ 20 mmHg in systolic or ≥ 10 mmHg in mean arterial pressures, requiring nursing interventions such as the stopping of ultrafiltration, administration of saline or moving patients to Trendelenburg position. IDH events are recorded in the nursing entries as above which will be used as a basis for coding this information.

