### Secondary outcomes

The secondary outcomes of this study are grouped in to following sub-categories:

A. Safety outcomes

To compare key indicators of patient wellbeing in those receiving incremental HD and conventional care over the 6-month follow-up period:Differences in mean pre-dialysis BPs and IDWG (or loss)Comparison of pre-dialysis potassium levels, serum albumin, PTH, adjusted calcium and phosphate levels.Numbers of AEs and SAEs (based on definitions in table S2)Numbers of hospitalisationsNumbers and rates of major adverse cardiovascular events (the 4p-MACE: a composite of cardiovascular deaths, nonfatal myocardial infarctions, nonfatal strokes and hospitalisations for unstable angina) [42]Numbers and rates of all-cause mortalityAnaemia management: differences in Hb, Ferritin, TSAT and doses of IV iron and erythropoietin stimulating agent (ESA.)

B. Mechanistic outcomes

To study changes in RRF, fluid load, performance status and quality of life over 6 months in patients receiving incremental HD (incremental HD group only). All these are relative to baseline:Change in RRF using urine volume, KRU and Cystatin C levelsChange in pre-dialysis fluid load as measured using BIS and Ntpro-BNPChange in KDQOL-SF v1.3 scores (including in its sub-domains)Change in Karnofsky performance index

C. Qualitative outcomes

To explore patients’ experiences of starting HD incrementally and of participating in the current study using semi-structured interviews—see interview sub-study section.

D. Further feasibility outcomes

To acquire data needed for planning a future RCT:Progression to HD: some patients recruited for the current study may not start HD within the study period (the timing of onset of dialysis can be unpredictable). Of the patients recruited from pre-dialysis clinics, the proportion of patients progressing to receiving incremental HD within the study period will be reported. This will inform the number of additional participants needed in a future RCT and the duration of recruitment period.Completion rates of the non-routine tests namely the 24-h urine collections, BIS and the KDQOL-SF v1.3 questionnaire.

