## Discussion

### Statement of novelty

We have proposed a novel and pragmatic study that simplifies incremental HD by focusing on key elements of patient welfare and safety using commonly used measures in the care of dialysis patients.

There is currently no agreement on the optimal method of implementing incremental HD and the term ‘incremental HD’ has been used variably in the past to describe twice-weekly treatment regimens of different aims and degrees of complexity [46–49]. In one version described by Kaja Kamal et al. [48], twice-weekly dialysis is administered on an ongoing basis as long as RRF is maintained above stdKt/V_urea_ > 2. This requires regular RRF measurements through timed urine collections and clinicians to react to changes in RRF and adjust dialysis prescriptions. Kaja Kamal et al. have previously reported that the patients spend a median of 9 months receiving incremental HD before transitioning to three-times weekly HD [48]. A trial of this regime is currently underway [50].

Our version of incremental HD is novel as we apply twice-weekly HD in a time-limited manner (i.e., the first 15 weeks of dialysis), which does not require time urine collections. In our regime, the key aim is to focus on reducing the risk of decompensation in the early days of dialysis, while patients are still adapting (and hence aiming to reduce the high rates of early mortality) which we hypothesise is related to intensity of dialysis [51]—our approach is in contrast to other therapy regimens [19, 46, 52] where the primary aim of treatment is to preserve RRF and hence influencing medium/long-term outcomes. Our regime is of a relatively short duration as we expect RRF to decline significantly [53, 54] in first few months of dialysis making twice-weekly HD unsustainable.

Other key features that distinguish this version of incremental HD from other solutions proposed previously[46, 50, 55, 56] include: simplified eligibility criteria (see Table 1) that pre-selects out-patient HD starters who are well prepared for dialysis; lack of adequate preparation [22, 57] significantly carry worse prognoses and such patients are not suitable for incremental HD. Note that previous studies have used more complex screening methods such as timed urine collections at baseline to select suitable candidates for incremental HD, but concerns have been voiced about completion and accuracy of urine collections in dialysis patients [58–60].

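### The blood pressure and fluid measures named for comparing the arms (pre-dialysis BP and IDWG) mix session spacing with fluid control and do not reflect session length

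*Protocol article*

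**What the plan says.** Secondary outcomes, part A, compares the arms over 6 months. Its blood pressure and fluid item is "Differences in mean pre-dialysis BPs and IDWG (or loss". Adverse events appear there as "Numbers of AEs and SAEs (based on definitions in table S2". In the same list, cardiovascular events and deaths are to be given as both numbers and rates.

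More is collected than is named for comparison. Under Weights and blood pressures, of the weight and BP readings: "These will be measured pre- and post-dialysis"; and "BP readings taken during dialysis (intra-dialytic BPs) will also be recorded". Safety and adverse events data defines intra-dialytic hypotension (a symptomatic fall in pressure that needs nursing intervention), gives a background figure ("Intra-dialytic hypotension is common and affects 17% of all dialysis sessions") and adds: "IDH events are recorded in the nursing entries as above which will be used as a basis for coding this information".

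The Analysis section summarises weights, pressures and IDWG as means by treatment phase. It leaves control mid-week readings out of those averages because controls dialysed three times a week. It also reports sessions per week and minutes per week by phase in both arms. All comparisons of secondary outcomes are descriptive.

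The regime begins, after a two-day start, with "twice-weekly 2-h long dialysis sessions for 2 weeks". Six weeks of two 3-h sessions a week and six weeks of three 3-h sessions a week follow. The Statement of novelty gives the rationale: the early decompensation that the regime aims to reduce is something "which we hypothesise is related to intensity of dialysis".

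**The concern.** The arms differ by design in how often and how long patients dialyse, so a safety measure that depends on the schedule will differ between them even if fluid control is identical. IDWG per interval is such a measure: a longer gap gives a larger gain. It also leaves out session length, so it does not show how fast the fluid has to come off. Pre-dialysis pressure is measured before the session and does not describe it.

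Two things are at stake. A higher IDWG in the incremental arm could reflect spacing alone, and the plan gives no per-day figure to separate the two. And the load within each session, which bears on whether a shorter and less frequent start is gentler, is not among the named comparisons although its inputs are recorded. The study looks for signals to help design a future randomised trial, so a comparison distorted by schedule weakens one of its uses.

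**Working it through.** The plan states no fluid-removal figure, so there is none to reproduce. The checks below are direct arithmetic for the schedule as prescribed. Phase 1 is left out because the plan describes it as like a conventional start.

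**Inputs.** Incremental schedule, from the intervention section: phase 2, 2 sessions of 2 h a week; phase 3, 2 of 3 h; phase 4, 3 of 3 h. Controls: 3 sessions a week (Analysis). Control session length L is not stated; I assume 3 to 4 h. Hypotension: 17% of sessions (Safety and adverse events data).

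**1. IDWG from spacing alone.** Assume the usual gaps: 3 and 4 days when twice weekly; 3, 2 and 2 days when three times weekly.
- Incremental mean gap: (3 + 4)/2 = 3.5 days.
- Control mean gap without the mid-week reading: (3 + 2)/2 = 2.5 days. Ratio 3.5/2.5 = 1.4.
- Control mean gap with all sessions: 7/3 = 2.33 days. Ratio 3.5/2.33 = 1.5.

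Dropping the mid-week readings reduces the artefact but does not remove it.

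**2. Fluid removed per hour at equal weekly gain.** Ratio = control hours per week / incremental hours per week = 3L/(sessions × hours), using all sessions.

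| Phase | Incremental h/week | L = 3 h (9 h/week) | L = 4 h (12 h/week) |
|---|---|---|---|
| 2 | 2 × 2 = 4 | 9/4 = 2.25 | 12/4 = 3.0 |
| 3 | 2 × 3 = 6 | 9/6 = 1.5 | 12/6 = 2.0 |
| 4 | 3 × 3 = 9 | 9/9 = 1.0 | 12/9 = 1.33 |

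In phase 2 the part that IDWG cannot show is the session-length factor L/2, which is 1.5 to 2.0.

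**3. If the incremental arm gains less fluid.** Let weekly gain be r times control, in phase 2.
- r = 0.75: removal per hour 0.75 × 2.25 = 1.69 to 0.75 × 3.0 = 2.25 times control; IDWG 0.75 × 1.4 = 1.05 times control.
- r = 0.5: removal per hour 0.5 × 2.25 = 1.125 to 0.5 × 3.0 = 1.5 times control; IDWG 0.5 × 1.4 = 0.7 times control.

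So IDWG could look similar or lower while removal per hour is higher.

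**4. Hypotension read as events per patient, phase 2 (2 weeks).** Sessions per patient: incremental 2 × 2 = 4; control 3 × 2 = 6.
- Control at 17%: 0.17 × 6 = 1.02 events.
- Incremental at the same risk: 0.17 × 4 = 0.68.
- Incremental risk that gives equal counts: 1.02/4 = 25.5%, and 25.5/17 = 1.5 times.
- Incremental at three times the risk: 0.51 × 4 = 2.04 against 1.02.

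Phase 3 has the same proportion (12 against 18 sessions), so the same 1.5 applies there.

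**The case against.** A reader might infer that haemodynamic safety rests on these two measures alone, and that load within sessions could triple unseen. The documents do not support that, for four reasons.

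- Intra-dialytic hypotension is defined and coded as safety data, and adverse events are reported in both arms. Table S2 is not shown, so its inclusion as an adverse event cannot be confirmed, but its placement makes that likely. A threefold per-session risk would be visible in the counts (2.04 against 1.02 per patient in phase 2).
- Threefold removal per hour needs a 4-h control session, equal weekly gain and phase 2, which lasts two weeks of a six-month follow-up. Extra sessions are also allowed, which would narrow the gap.
- The Analysis section summarises weights and pressures by phase without restricting them to pre-dialysis values. With minutes per week also reported, a crude hourly rate could be worked out for each arm.
- The rationale speaks of dialysis intensity in general, and the study's formal test is recruitment and retention.

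It can also be said that derived variables are often left to an analysis plan, and that no rule says a higher IDWG will be read as harm.

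These points dispose of the strong reading. They do not repair the named comparison. IDWG per interval stays schedule-dependent after the mid-week rule. Mean pressures would not isolate what happens during a session. Adverse events listed as numbers carry no session denominator. The article fixes these measures, so this is a matter of choice of metric and not only of omitted detail.

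**Conclusion.** The point holds in a limited form. The named blood pressure and fluid comparators are confounded by spacing and blind to session length. Spacing alone gives an IDWG ratio of about 1.4 in the twice-weekly phases under the planned mid-week rule. The hourly-removal ratios are upper bounds: they rest on equal weekly gain, the schedule as prescribed and an assumed control session of 3 to 4 h.

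Hypotension is not ignored, but a per-session excess of up to about 1.5 times in the twice-weekly phases could be cancelled by the smaller number of sessions if events are read per patient. This is a weakness in how safety data will be compared. It is not evidence that the regime is unsafe, and it does not affect the primary outcome.

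**What to change.** In Secondary outcomes part A and in Analysis, add three descriptive summaries by arm and treatment phase:

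- IDWG per interdialytic day, alongside IDWG per interval.
- Fluid removed per hour per kg: (pre-dialysis weight − post-dialysis weight) / session hours / post-dialysis weight.
- Intra-dialytic hypotension events divided by sessions delivered.

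Say for each whether control mid-week sessions are included, and report how complete the control data are.

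The cost is analysis wording and a few derived variables. Pre- and post-dialysis weights, treatment time and hypotension events are already to be recorded or extracted. Nothing changes in treatment, visits or sample size, and no formal tests are added. Two limits should be stated with the results: control records may be incomplete, and weight change only approximates fluid removed because intake or saline during a session alters it.

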### Sample size

As this is a feasibility study, a formal sample size calculation has not been performed. The recruitment target is 20 participants in the active interventional arm and 40 in the historical control group (1:2 matching).

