### Follow-up

Participants will be followed-up for 6 months from the start date of HD therapy (see Fig. 1 above). A total of eight study visits will be carried out for each participant as per the schedule presented in supplementary table S1. Participant monitoring, and data collection is more intense in the first 2 weeks.

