#### Blood tests

In routine dialysis practice, the drawing of ‘monthly bloods’[26] involve regular measurements of full-blood count (FBC), serum biochemical profile (BCP) and C-reactive protein (CRP), and 3-monthly measurements of serum Ferritin, Transferrin Saturations (TSAT) and Parathyroid hormone (PTH) levels. We will utilise these routine tests when making selected comparisons between patients in the two treatment arms (see outcomes). Bloods samples are drawn at the first dialysis session of each calendar month. Urea reduction ration (URR) and eKt/V_urea_ are calculated monthly using the pre- and post-dialysis serum urea levels [27].

Additional (non-routine) pre-dialysis BCP testing will be carried out on days 7, 10 and 14 of dialysis to ensure close monitoring of serum potassium levels during the first 2 weeks of treatment.

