**Fig. 2 Fig2:**
[figure not shown]
Incremental HD regimen used in the study showing the incremental steps

Results of routine tests (including Hb, potassium, albumin, PTH, adjusted calcium, phosphate), and IV iron and ESA doses administered will be summarised (as mean and SD or median and inter-quartile range as appropriate) for each treatment phase. For patients in incremental HD group, urine volumes, KRU, serum Cystatin C levels, pre-dialysis overhydration measured through BIS (expressed in millilitres), NT-pro-BNP levels will be summarised as means or medians as appropriate for each measured time point (baseline, 1-, 3- and 6-month). Differences in these measurements over the follow-up period will be compared to their baseline values.

Numbers of deaths from all causes, hospitalisations, the 4-point major adverse cardiovascular events (4p-MACE: a composite of cardiovascular deaths, nonfatal myocardial infarctions, nonfatal strokes and hospitalisations for unstable angina), AEs and SAEs will be reported for both the treatment arms.

Formal statistical tests will not be undertaken on secondary outcomes due to the feasibility design of this study (descriptive comparisons will, however, be drawn to examine findings for potential signals).

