As above, we have also bypassed the need for timed urine collections in the follow-up period by introducing monitoring measures that focus on key safety parameters (i.e. additional tests for hyperkalaemia and hydration status). This approach opens incremental HD to a wider section of new dialysis starters, particularly to the elderly. We pre-specify fixed increments in HD treatment times, providing more certainty to patients and helping dialysis staff with the planning of treatments.

The use historical controls is novel in dialysis research. A control arm is needed to compare the rates of pre-defined safety events, and to study the impact of incremental HD on selected patient outcomes. The delivery of modern HD therapy is highly regimented and treatment records are readily accessible through dedicated dialysis databases. This makes the use of historical controls a feasible option, particularly when examining rates of well-recognised events such as changes in pre-dialysis weights, BPs, episodes of hyperkalaemia and details of medical interventions. Our strategy hence represents a pragmatic approach which also increases the study power when comparing selected (the routinely collected) parameters [61, 62] and ensures timely completion of the study provided there is appropriate matching of key confounding attributes [63].

To our knowledge, this is the first study exploring the views of patients receiving incremental HD through recognised qualitative research methods. Analysing patient experiences are an important aspect of gauging future demand for incremental HD and forms key part of the feasibility works conducted here. The qualitative methods in this study will also aid in achieving a deeper understanding behind some of the quantitative findings (e.g., dropout rates) making these findings much more informative.

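### AEs, SAEs and hospitalisations are set as bare numbers across arms of 20 and 40, and no rule limits the event comparison to a source that both arms share

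*Protocol article*

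**What the plan says.** Under Secondary outcomes, A. Safety outcomes, the protocol article sets out a comparison of the two arms over 6 months. In that list MACE and all-cause mortality are to be given as numbers and rates. Hospitalisations are given as numbers only, and so are adverse events: "Numbers of AEs and SAEs (based on definitions in table S2". After Fig. 2, the Analysis section covers deaths, hospitalisations, MACE and adverse events in one sentence, as numbers throughout, ending "AEs and SAEs will be reported for both the treatment arms". The Statement of novelty describes the purpose differently: "A control arm is needed to compare the rates of pre-defined safety events".

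On size and follow-up: "The recruitment target is 20 participants in the active interventional arm and 40 in the historical control group (1:2 matching", and "Participants will be followed-up for 6 months from the start date of HD therapy".

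On how events come to light, the incremental arm is watched more closely. Under Safety and adverse events data: "in the first month, five study related checks are undertaken including review by the study medic on four occasions". Under Blood tests: "Additional (non-routine) pre-dialysis BCP testing will be carried out on days 7, 10 and 14 of dialysis". Control data are extracted from past dialysis records, nursing notes and medical history (Recruitment for control arm). For participants, too, the nursing record is searched for events and checked against the electronic health record.

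**The concern.** The three sections do not agree on the measure. If the numbers wording is followed, counts from a smaller arm stand beside counts from one twice its size, and the smaller arm looks safer without being so. The protocol notices unequal measurement elsewhere: controls' mid-week blood pressures and weights are left out of the averages, and selected between-arm laboratory comparisons use routine tests. It states no matching rule for events.

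Rates alone would not settle the matter. Extra visits and extra potassium samples in one arm can raise that arm's recorded non-serious AEs and hyperkalaemia at equal true risk. The Statement of novelty names hyperkalaemia episodes among the events for which historical controls are suited, so this touches an intended comparison. No formal tests are planned on secondary outcomes. What is at stake is therefore the descriptive reading for signals, in a study meant to test safety and to shape the regimen of a later RCT.

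**Working it through.** **Inputs.** 20 participants and 1:2 matching (Sample size); 6 months, taken as 26 weeks (Follow-up); the phases in The intervention; controls on three sessions a week from the outset (Analysis); IDH in 17% of sessions (Safety and adverse events data); monthly routine bloods (Blood tests).

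**The plan's own figure.** 20 × 2 = 40 controls, as stated.

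**1. Arm size.** At equal risk per patient and equal follow-up, the raw count ratio is 20/40 = 0.50; per patient-month it is 1.00. Equal raw counts would mean a 2.0-fold rate in the incremental arm. Patients do not all contribute equal time either. The retention threshold of 70% would be met with 0.70 × 20 = 14 completers, so up to 6 of 20 could contribute less than 6 months. Patient-time is therefore a better denominator than heads.

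**2. Scheduled sessions.** The start phase has 2 sessions ("day 1, 2-h HD session; day 2, 3-h HD session"). Phase 2 has 2 × 2 = 4, phase 3 has 2 × 6 = 12 and phase 4 has 3 × 6 = 18, which makes 36. Phases 2–4 fill 14 weeks, so the programme takes 14 or 15 weeks depending on whether the start days count as a week of their own. Assuming three sessions a week afterwards:

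- 15 weeks: 36 + 11 × 3 = 69 sessions per patient
- 14 weeks: 36 + 12 × 3 = 72 sessions per patient
- controls: 26 × 3 = 78 sessions per patient

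69/78 = 0.88 and 72/78 = 0.92, so 8–12% fewer. The gap lies early: phases 2–3 have 4 + 12 = 16 sessions against 8 × 3 = 24.

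**3. IDH with no true difference, 17% per session in both arms.**

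| Period | Incremental | Control | Ratio |
|---|---|---|---|
| 6 months, count | 20 × 69 × 0.17 = 235 to 20 × 72 × 0.17 = 245 | 40 × 78 × 0.17 = 530 | 0.44–0.46 |
| 6 months, per patient | 11.7–12.2 | 13.3 | 0.88–0.92 |
| Phases 2–3, count | 20 × 16 × 0.17 = 54 | 40 × 24 × 0.17 = 163 | 0.33 |
| Phases 2–3, per patient | 2.7 | 4.1 | 0.67 |
| Per session | 0.17 | 0.17 | 1.00 |

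The common 17% is illustrative; it ignores any effect of session length.

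**4. Detection.** In the first 14 days the incremental arm has three added biochemistry tests. Routine draws average 14/30.4 = 0.46 per patient if start dates are spread evenly over the month. How many more events this finds is not in the documents. Assume, for illustration only, that detection is 1.25 to 2.0 times higher at equal true risk. The raw count ratio is then 1.25 × 0.50 = 0.63 to 2.0 × 0.50 = 1.00, and the rate ratio per patient-time is 1.25 to 2.0. Moving to rates removes the factor 0.50 and leaves the detection factor fully visible. The two changes are needed together.

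**The case against.** The best defence is that this is a matter of wording. The discussion already speaks of rates, the denominators are stated, and delivered sessions per week are reported by phase, so anyone can divide. The primary outcome is recruitment, and the feasibility thresholds do not use event counts. This limits the consequence, but it does not reconcile three sections that name different measures, and nominal arm size is not patient-time when some patients leave early.

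Several stronger readings are tempting and are not supported:

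- A reader might infer a three-fold distortion in IDH. That figure holds only for phases 2–3, and it is a factor 2.0 from arm size times 1.5 from sessions. The outcomes are compared over 6 months.
- A reader might treat the lower session count as bias. Fewer sessions are the intervention, and fewer IDH episodes per patient would be a real reduction in burden. For hospitalisations and SAEs, patient-time is the natural denominator. Clinicians may also add sessions, so the scheduled gap need not be the delivered one.
- A reader might infer that events are found by wholly different means. The nursing record, with the electronic record, already serves participants, IDH is coded from nursing entries, and the same kind of record is extracted for controls. Hospitalisations are unlikely to be missed in either arm.
- A reader might conclude that hyperkalaemia will look worse. The documents support only that it can. Whether an isolated raised potassium counts as an AE depends on supplementary table S2, which is not among the documents at hand.

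**Conclusion.** The point holds in limited form. The Secondary outcomes and Analysis sections fix AEs, SAEs and hospitalisations as numbers, against the stated purpose of comparing rates. At equal risk and equal follow-up, those numbers stand at 0.50. For session-linked events the 8–12% shortfall in scheduled sessions makes it 0.44–0.46, assuming three sessions a week after the programme. Surveillance works the other way for non-serious AEs and hyperkalaemia, by an amount that cannot be derived; the 1.25 to 2.0 range above is an assumption. The documents do not support a claim that every listed event is distorted, or that the plan is uniformly one of raw counts. The damage is to descriptive signal reading, not to an error rate or to the primary outcome. The change should be made because it is cheap and because safety against conventional HD is a main reason for having controls.

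**What to change.** - Align Secondary outcomes, Analysis and the Statement of novelty: give AEs, SAEs, hospitalisations, MACE and deaths in both arms as numbers and as events per patient-month.
- Report IDH both per session (risk of a session) and per patient-time (burden on the patient).
- Base the between-arm comparison on events found in the source common to both arms: dialysis nursing record, electronic record and routine bloods.
- List separately, for the incremental arm, events found only through study visits or study bloods. The flag should record how the event first came to light, because an event found on a study sample may also be written into the nursing record.

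The cost is wording in three sections, one source flag per event and slightly fewer events in the comparison. No new data collection is needed.
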